#### Secondary analyses

1. An analysis identical to the primary analysis, studying mortality at 28 days taking an alpha risk of 0.05.

2. Average length of ICU stay and in-hospital stay will be described and compared for survivors.

3. The number of days without mechanical ventilation and the number of days without RRT in the two groups will be compared. Deceased patients are considered as having a number of days without mechanical ventilation and without RRT equal to zero. The numbers of days will be compared in both groups using a Mann–Whitney test.

4. Dependence on dialysis at hospital discharge will be compared between groups using the chi-squared or Fisher’s exact test. If the groups appear imbalanced in terms of the pre-existence of non-dialyzed chronic renal failure or administration of nephrotoxic drugs, then logistic regression will be performed to adjust for these factors.

5. The frequency of occurrence of at least one episode of hypotension requiring the introduction or increase of noradrenaline, pulmonary edema due to overload, cardiac arrhythmias (ventricular tachycardia, ventricular fibrillation, torsade de pointes and atrio-ventricular block grade III), severe metabolic disorders and blood transfusions (≥3 units of packed red blood cells) will be compared between groups using the chi-squared or Fisher’s exact test.

6. The number and characteristics of patients in the delayed RRT group for whom the occurrence of a criterion for emergency RRT was observed will be described.

These comparisons will be performed by ITT and per protocol. All analyses will be performed using SAS Version 9.2 (SAS Institute Inc, Cary, NC, USA) by the team of statisticians at the CIC-EC of the University Hospital of Dijon, France. The significance level is set at 0.05 for all final analyses.

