#### Sample size calculation

It has been shown that the mortality of septic shock patients who develop AKI is around 50%. Assuming an absolute reduction in mortality of 10% (55% mortality at 90 days in the delayed RRT group versus 45% in the early RRT group), 864 patients (432 per group) are required to ensure 80% power at a bilateral alpha risk of 0.05, assuming a rate of 5% non-evaluable cases.

The expected reduction of 10% in mortality was chosen as a clinically relevant difference by the study team. There are currently no data in the literature that could serve as a precedent for this, due to wide variations between existing studies in the types of patients included, the definitions of AKI used, and the definition of what constitutes early or late treatment. In light of the heterogeneous data available, a conservative estimate of a 10% reduction was retained as being clinically relevant.

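### Length of stay is tested between arms in survivors only, in a trial designed to change who survives; the test should include deaths

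*Protocol article*

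**What the plan says.** The protocol article, under Secondary analyses, treats death in different ways in adjacent items.

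- Item 2 (stay): "Average length of ICU stay and in-hospital stay will be described and compared for survivors". The time at which survival is judged (ICU, hospital or day 90) is not given, and no test is named.
- Item 3 (ventilator-free and RRT-free days): "Deceased patients are considered as having a number of days without mechanical ventilation and without RRT equal to zero".
- Item 4 (dialysis): "Dependence on dialysis at hospital discharge will be compared between groups", by chi-squared or Fisher's exact test. No denominator or rule for in-hospital deaths is given. An adjusted analysis is conditional: "If the groups appear imbalanced in terms of the pre-existence of non-dialyzed chronic renal failure or administration of nephrotoxic drugs, then logistic regression" is then to be run.

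The section ends by applying intention to treat and per protocol to all these comparisons, at a significance level of 0.05. The Objectives section lists ICU and hospital stay among the key secondary endpoints, and RRT dependence at discharge under efficacy and safety. The Sample size calculation assumes "55% mortality at 90 days in the delayed RRT group versus 45% in the early RRT group".

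**The concern.** Randomisation makes the arms comparable as randomised. It does not make the survivors of each arm comparable once treatment affects survival. If early RRT works as hypothesised, its survivors include patients who would have died under delayed RRT. Should those patients stay longer, the average in early-arm survivors rises although no one who would have survived anyway stays a day longer.

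The comparison therefore loses the protection of randomisation in the scenario the trial hopes for. Stay is a key secondary endpoint, and readers may weigh a longer stay against a mortality benefit. Item 3 shows that the authors had a way to keep deaths in the analysis and did not use it for stay.

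Dialysis dependence at discharge raises a related question of reading. A patient who dies in hospital cannot leave dependent, so the result is hard to interpret apart from mortality. Separately, making the adjustment depend on an undefined judgement of imbalance leaves open whether an adjusted result will exist.

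**Working it through.** **Inputs from the Sample size calculation.** "864 patients (432 per group) are required", with "80% power at a bilateral alpha risk of 0.05", "assuming a rate of 5% non-evaluable cases", and mortality of 55% versus 45%.

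**Reproducing the plan's figure.** A two-proportion calculation with continuity correction gives 412 per arm. Allowing for 5% non-evaluable, 412 / 0.95 = 433.7, so 434 per arm (868 in total); 412 × 1.05 = 432.6, so 433 per arm (866). Both are close to 864, so 55% and 45% are the operative design rates. The plan gives no figure for stay or dialysis dependence.

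**Step 1: who the survivors are.**
- Delayed: 432 × 0.45 = 194.4
- Early: 432 × 0.55 = 237.6
- Difference: 43.2, which is 43.2 / 237.6 = 18% of early survivors

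Assume that early RRT causes no death that delayed RRT would have avoided. Then 45% of patients survive in either arm and 10% survive only with early RRT (the extra survivors). The documents give no ICU or in-hospital mortality, so 90-day mortality stands in for it.

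**Step 2: stay (all stays are assumptions).** Let A be mean stay in patients who survive either way, the same in both arms, and X the mean in extra survivors.
- Early survivors: (0.45A + 0.10X) / 0.55. Delayed survivors: A.
- Difference: (0.10 / 0.55)(X − A) = 0.18(X − A)
- A = 12, X = 20: (5.4 + 2.0) / 0.55 = 13.5 versus 12.0, or +1.5 days
- A = 12, X = 25: (5.4 + 2.5) / 0.55 = 14.4 versus 12.0, or +2.4 days
- A = 20, X = 30, 40, 50: +1.8, +3.6, +5.5 days
- X = A: 0

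If the mortality effect were half the planned one (55% versus 50%), the factor is 0.05 / 0.50 = 0.10, and the first two results become 0.10 × 8 = +0.8 and 0.10 × 13 = +1.3 days. If X is below A, the sign reverses.

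**Step 3: how often this would reach p < 0.05.** Simulation of 4,000 trials per setting, 432 per arm, lognormal stay (SD of log 0.8), Mann–Whitney test assumed. Stay is unchanged throughout in patients who survive either way.

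| Stay of extra survivors relative to others | Survivors-only test significant |
|---|---|
| 1 | 4.9% |
| 1.5 | 14% |
| 2 | 31% |
| 2.5 | 48% |

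**Step 4: dialysis dependence (rates are assumptions).** Take 10% in patients who survive either way, and 10%, 30% or 50% in extra survivors. For 30%, the early arm has 0.45 × 0.10 + 0.10 × 0.30 = 7.5% of those randomised alive and dependent; the delayed arm has 0.45 × 0.10 = 4.5%.

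| Rate in extra survivors | Survivors only, early v delayed | All randomised, deaths not dependent | Death or dependence |
|---|---|---|---|
| 10% | 10.0% v 10.0% | 5.5% v 4.5% | 50.5% v 59.5% |
| 30% | 13.6% v 10.0% | 7.5% v 4.5% | 52.5% v 59.5% |
| 50% | 17.3% v 10.0% | 9.5% v 4.5% | 54.5% v 59.5% |

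In simulation the survivors-only test is significant in about 21% of trials at 30% and 58% at 50%. Size, and in part direction, depend on how deaths enter.

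**The case against.** Several points against the concern stand.

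- **The bias is conditional.** It needs a difference in mortality (or in survivors' case mix) and extra survivors whose stay differs. The 10-point gap is a planning hypothesis. A reader might infer that the extra survivors must be the sickest; that is plausible, but nothing in the documents establishes it.
- **Significance is not the usual result.** With stays 1.5 to 2 times as long, 14% to 31% of simulated trials reject, so most would not report a significant difference.
- **Item 4 is silent rather than wrong.** A reader might infer that it mishandles death. It states no wrong rule, and a condensed article may leave the denominator to the full protocol or analysis plan.
- **A dialysis difference need not be an artefact.** A reader might infer that excess dependence would appear with no such effect in any patient. In the 30% example, 7.5% versus 4.5% of randomised patients leave alive and dependent. That increase is real, although the additional patients would otherwise have died.
- **The composite has its own weakness.** Death supplies 45 of the 52.5 points and 55 of the 59.5, so it largely repeats the primary outcome.
- **The adjustment is mostly specified.** The unadjusted test is always done and both covariates are named. To say that the data choose the model goes too far; the data decide only whether the adjusted analysis is run.
- **There is mitigation.** Mortality is tested separately at 90 and 28 days, and RRT-free days already include deaths.

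None of this answers item 2. Its survivors-only rule is explicit, so it is not a detail awaiting another document.

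**Conclusion.** The point holds for item 2 in conditional form. A between-arm test of stay restricted to survivors is not protected by randomisation if the trial changes mortality. At the design rates, the distortion is 0.18 times the excess stay of the extra survivors: 1.5 to 2.4 days under the stays assumed in the main illustration, and none if mortality is unaffected or the extra survivors resemble the others. This rests on assumed stays, on 90-day mortality standing in for in-hospital mortality, and on no patient being harmed by early RRT.

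The documents do not support the stronger conclusion that both the stay and the dialysis comparisons are certain to be biased. For item 4 the supportable point is about presentation: dependence should not be read apart from death, and the adjustment should not hang on an undefined trigger. Both endpoints are secondary; the primary mortality analysis and the sample size stand.

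**What to change.** 1. **Item 2.** Make the between-arm test death-inclusive in all randomised patients. Either compare days alive and out of ICU, and out of hospital, to day 90 with deaths set to zero (the convention of item 3), or compare the cumulative incidence of discharge alive with death as a competing event. Keep stay in survivors as description, without a test, and say at what time survival is judged.
2. **Item 4, reporting.** Show dialysis dependence together with death: the composite of death or dependence, with both components by arm.
3. **Item 4, adjustment.** Prespecify the adjusted analysis for pre-existing chronic renal failure and nephrotoxic drugs at enrolment, and delete the imbalance condition. Enrolment exposure is the right covariate because later exposure may be affected by treatment.

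**Cost.** A change of wording and a little more analysis. The article already provides for follow-up of death, hospital discharge and RRT need, and for recording comorbidities and nephrotoxic drugs at enrolment; discharge dates are needed for the planned stay endpoint anyway. The article does not mention readmissions, so if they are not recorded, days out of hospital should be counted from first discharge alive. The price is a different estimand for stay and a composite driven mainly by death, which is why its components must be shown. No extra patients are needed.

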#### Acute renal failure

AKI will be defined and classified according to the RIFLE criteria (risk of renal dysfunction, injury to the kidney, failure of kidney function, loss of kidney function and end-stage kidney disease) as outlined by the Acute Dialysis Quality Initiative (ADQI) Working Group [23]. In brief, the RIFLE criteria classify AKI into three categories of severity (risk, injury and failure) and two categories of clinical outcome (loss and end-stage kidney disease) based on relative changes to serum creatinine and urine output. The presence of AKI will be defined by the failure stage of the RIFLE classification, namely an abrupt (within 7 days) reduction in kidney function, characterized by a threefold increase in serum creatinine relative to baseline; an absolute value ≥354 μmol/L (accompanied by an acute increase ≥44.2 μmol/L); a reduction in urine output of ≤0.3 mL/kg/hr for ≥24 hr; or anuria for ≥12 hr. If pre-hospital baseline serum creatinine is unavailable, baseline serum creatinine is estimated based on back-calculation of the abbreviated Modification of Diet in Renal Disease (MDRD) as recommended by the ADQI [23].

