#### Randomization

Randomization is performed during the first 48 hr of septic shock after the development of at least one criterion defining the failure grade of the RIFLE classification. Randomization takes place after verification of the eligibility criteria, following an online request by the investigator using Tenalea® software (Formsvision BV, Abcoude, Netherlands). This allocation is based on a minimization technique taking into account the center, age, sequential organ failure assessment (SOFA) score, site and type of infection. Patients are randomly assigned to one of the two groups in a 1:1 ratio. Due to the nature of the study intervention, blinding is not possible. However, the CIC-EC (Dijon) will manage all the data and generate blinded reports for the Data Safety and Monitoring Board. The investigators at the participating sites will remain unaware of study group outcomes until the database is locked.

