### Data collection

Detailed clinical procedure-related RRT parameters, and physiologic and laboratory data will be collected. Blood and urine will be collected at baseline, 12, 24, 36 and 48 hr and once daily thereafter until the study participants are discharged from ICU. Data will be collected on standardized case report forms (CRFs). All adverse events will be recorded on the CRF on specific pages reserved for this purpose. A simplified procedure will be used for foreseeable adverse events (hemodynamic instability, rhythm disturbances, electrolyte or acid-base imbalance, and bleeding events related to hemodialysis catheters or anticoagulants). Adverse events will be considered as serious if they cause death, are life-threatening, cause hospitalization (or prolongation of initial hospitalization), cause disability or cause permanent damage, a congenital anomaly or birth defect. Investigators must report any serious adverse event to the sponsor (the University Hospital of Dijon, France) promptly by email or telephone, followed by a written report within 48 hr. Completed CRFs will be returned to the CIC-EC and entered into a secured central database for independent quality control and centralized analysis.

Clinical data obtained will include demographic characteristics, comorbidities and prescribed and current drug therapy. Details of admission diagnoses, surgical status, and dates of hospital and ICU admission will be recorded. Detailed data on AKI and on septic shock will be recorded on the date of enrollment: interventions (i.e. mechanical ventilation, vasoactive drugs and fluid therapy), hemodynamics (i.e. blood pressure, heart rate and central venous pressure), nephrotoxic drugs (e.g. aminoglycosides, radiocontrast agents and hydroxy-ethyl starch), details of sepsis (i.e. site of infection and effectiveness of antimicrobial therapy) and acute physiology (i.e. components of severity of illness and SOFA score, simplified acute physiology score (SAPS II), urine output, fluid balance and secondary non-kidney organ dysfunction). During the trial, data will be collected on daily urine output, fluid balance, electrolytes, acid-base status, serum creatinine and urea, and components of the SOFA score. Data will be collected each day on whether the primary endpoint (mortality) has occurred, for evidence of any secondary endpoints and for criteria for trial discontinuation. Finally, any study protocol violations will be recorded.

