### Statistical analysis

All enrolled patients will be included in the main population analysis. The primary analysis will be by intention to treat (ITT). The characteristics of the two groups will be compared using the usual univariate tests (chi-squared or Fisher’s exact test for categorical variables, and analysis of variance or Mann–Whitney test for quantitative variables, as appropriate). The main comparison of the proportion of deaths at 90 days in both treatment groups will be performed using Fisher’s exact test, with secondary analysis by the Kaplan–Meier method, comparison using the log rank test, and Cox regression.

For the per-protocol analysis, patients will be grouped according to the time of initiation of the RRT. If RRT is initiated within 12 hr after the onset of the failure stage according to the RIFLE classification, then the patient will be included in the early RRT group. Conversely, if RRT is initiated >12 hr beyond this period, the patient will be included in the delayed RRT group. The per-protocol analysis will use the same techniques as the ITT analysis.

If the ITT and/or per-protocol analyses show a benefit of early (<12 hr) initiation of RRT, a secondary analysis will be performed using an extension of the proportional hazards model proposed by Abrahamowicz and MacKenzie [31] to estimate the non-proportional and non-log-linear effects, taking into account the exact time since initiation of RRT. This model will make it possible to trace the effect of initiation of RRT over time, thus visualizing whether early initiation results in lower risk of death after adjusting for major confounders, taking into account any non-proportional and/or non-log-linear effects. The main conclusion of the test will only cover the ITT analysis. Two interim analyses will be performed after the inclusion of, respectively, 200 and 400 patients.

Safety will be analyzed by assessing the frequency of arterial hypotension requiring the introduction or increase of noradrenaline, pulmonary edema due to overload, cardiac arrhythmias (ventricular tachycardia, ventricular fibrillation, torsade de pointes and atrio-ventricular block grade III), severe metabolic disorders and blood transfusions (≥3 units of packed red blood cells) in both groups and comparing rates using the appropriate tests, with an alpha risk set at 0.05.

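### Adjustment of dialysis dependence for chronic renal failure and nephrotoxic drugs should be pre-specified, not triggered by observed imbalance

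*Protocol article*

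**What the plan says.** Item 4 of Secondary analyses in the Protocol article sets an unconditional comparison, by a chi-squared or Fisher test: "Dependence on dialysis at hospital discharge will be compared between groups using the chi-squared". It then makes a further step conditional: "If the groups appear imbalanced in terms of the pre-existence of non-dialyzed chronic renal failure or administration of nephrotoxic drugs". What follows when that condition is met is a second, adjusted analysis: "then logistic regression will be performed to adjust for these factors". The item does not say which result is to be believed if the unadjusted and adjusted analyses disagree, or whether the nephrotoxic drugs are those given before or after randomisation.

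Three other places bear on this:

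- Randomization describes allocation by a "minimization technique taking into account the center, age, sequential organ failure assessment (SOFA) score, site and type of infection". Pre-existing renal disease is not among these factors.
- Statistical analysis says "The characteristics of the two groups will be compared using the usual univariate tests", which is one way the trigger might be applied.
- Data collection says "Clinical data obtained will include demographic characteristics, comorbidities and prescribed and current drug therapy", and it lists nephrotoxic drugs among the details recorded on the day of enrolment. Both covariates are therefore available at baseline.

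**The concern.** By naming the two factors, the protocol signals that it regards them as relevant to leaving hospital on dialysis. Whether they enter a model nevertheless depends on how the arms turn out to look. This has two consequences.

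First, when the trigger fires there are two results for one endpoint and no order of precedence. They are not two versions of the same number: the unadjusted odds ratio is marginal and the adjusted one is conditional, and these differ when the covariate is prognostic, even with perfect balance.

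Second, when the trigger does not fire, a possibly strong predictor is left out. Under randomisation, imbalance in a baseline factor arises only by chance, so a significance-type trigger will seldom fire and the factor will usually be unused.

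Dialysis dependence at discharge is named in the abstract and in the objectives, so its analysis should be fixed in advance.

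**Working it through.** **Inputs from the document.** 432 patients per group, allocated 1:1; assumed 90-day mortality 55% and 45%; significance level 0.05. The protocol gives no figure for dialysis dependence, so there is no stated figure to reproduce for this endpoint. The total of 864 serves only as background. The continuity-corrected two-proportion formula gives 412 per arm; 412/0.95 = 433.7, so 434 per arm and 868 in total, close to 864.

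**Assumptions not in the document.** 216 survivors per arm (432 × 0.50, the midpoint of the two mortality assumptions, taken as those assessed at discharge); dependence 10% in control patients without chronic renal failure; prevalence of chronic renal failure 10, 15 or 30%; its odds ratio for dependence 3, 6 or 10; treatment odds ratio 1 or 2. The phrase about apparent imbalance is read as a baseline difference with p < 0.05. Only one binary covariate is modelled. Each scenario has 4000 simulated trials, comparing the unadjusted chi-squared test with logistic regression adjusted for the covariate.

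**Power at a treatment odds ratio of 2 (%)**

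| Prevalence | Covariate OR | Unadjusted | Adjusted only if imbalanced | Always adjusted | Gain from always adjusting (points) | Verdicts differ (% of trials) |
|---|---|---|---|---|---|---|
| 10% | 3 | 72.4 | 72.3 | 71.9 | −0.5 | 4.5 |
| 10% | 6 | 70.6 | 70.8 | 72.6 | 2.0 | 7.4 |
| 10% | 10 | 67.7 | 67.9 | 73.2 | 5.5 | 11.1 |
| 15% | 3 | 73.4 | 73.5 | 74.5 | 1.1 | 5.0 |
| 15% | 6 | 71.6 | 71.7 | 74.5 | 2.9 | 8.6 |
| 15% | 10 | 67.1 | 67.5 | 74.9 | 7.8 | 13.3 |
| 30% | 3 | 76.9 | 77.1 | 77.6 | 0.7 | 5.4 |
| 30% | 6 | 76.4 | 77.1 | 81.3 | 4.9 | 9.6 |
| 30% | 10 | 68.3 | 69.5 | 79.3 | 11.0 | 15.8 |

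The gain is the always-adjusted column minus the unadjusted column. The last column is the share of trials in which the adjusted and unadjusted tests fall on opposite sides of 0.05. The conditional rule recovers at most 69.5 − 68.3 = 1.2 points, because the trigger fires in only about 5% of trials (4.4 to 5.6%).

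**Effect estimate.** The mean unadjusted log odds ratio ranged from 0.530 to 0.685, that is exp(0.530) = 1.70 to exp(0.685) = 1.98. The adjusted estimate averaged about 2.0.

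**Type I error (treatment odds ratio 1).** Under the p < 0.05 trigger it was 4.0 to 5.3%. If the analyst could report whichever of the two tests was significant, it was 5.2 to 8.0%. Among trials where the covariate happened to be imbalanced at p < 0.05, the unadjusted test rejected falsely in 3 to 16%. That last range rests on about 0.05 × 4000 = 200 trials per scenario and is imprecise.

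**Standard error.** On the log-odds scale it rises with adjustment, for example from 0.278 to 0.301 (prevalence 10%, covariate OR 10, no treatment effect). Any gain is therefore in power.

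**Size of chance imbalance.** At 15% prevalence the SD of the difference is sqrt(2 × 0.15 × 0.85/216) = 3.4 points, with a 95% range of about ±6.7. If dependence were 50% with and 10% without chronic renal failure (odds ratio 9), a 6.7-point imbalance would shift the arm difference by 0.067 × 0.40 = 2.7 points. The pooled rate would be 0.15 × 0.50 + 0.85 × 0.10 = 16%, and the SE of the difference sqrt(2 × 0.16 × 0.84/216) = 3.5 points.

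**The case against.** The strongest reply is that nothing here is left open in a harmful way. The unadjusted test is always done, the two covariates and the model are named in advance, and the trigger looks at covariates and not at outcomes. The threshold is ordinary SAP content, and the planned univariate comparison of characteristics may supply it. The endpoint is secondary, and the trial's main conclusion is confined to the intention-to-treat analysis.

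Most of this stands, and it rules out several stronger readings that a reader might infer:

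- *That the crude result may be dropped in favour of the adjusted one.* Item 4 makes the crude comparison unconditional; only the added analysis is conditional.
- *That the open-label design lets someone set the trigger after seeing results.* Randomization says that site investigators stay unaware of outcomes by group until database lock, and the coordinating centre's statisticians do the analysis.
- *That the false-positive rate is materially inflated.* Under a fixed trigger it is not. Inflation needs a choice made on significance, which the text does not license.
- *That standard errors suffer.* For the planned logistic model the standard error rises with adjustment.
- *That a hidden imbalance would bias the result badly.* On the assumed rates, even a 6.7-point imbalance shifts the difference by less than one standard error, and an imbalance of that size could itself trigger adjustment.
- *That eligibility or minimisation is at fault.* The criterion of "an absolute value ≥354 μmol/L (accompanied by an acute increase ≥44.2 μmol/L" is part of the failure-stage definition that the trial adopted. Leaving a predictor of one secondary endpoint out of the minimisation is a legitimate choice.

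The missing threshold is not the point either. Whatever threshold an SAP supplied, observed balance would still decide whether the adjusted analysis exists.

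**Conclusion.** The point holds as a low-cost improvement to one secondary endpoint. Item 4 lets observed balance decide whether an adjusted analysis of dialysis dependence exists, states no precedence when there are two results, and leaves its own named factors unused when the arms look similar.

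The cost is mainly power. Under the assumptions listed it is about 0 points for a weak covariate (odds ratio 3), 2 to 5 points at 6, and 5.5 to 11 points at 10. In the same scenarios the adjusted and unadjusted tests disagree on significance in 4.5 to 16% of trials, so precedence matters. None of the prevalence, dependence or survivor figures comes from the document. If chronic renal failure is only weakly prognostic, the gain in power vanishes and only the clarity of a single pre-specified analysis remains. The 90-day mortality comparison is not affected.

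**What to change.** Replace the conditional sentence in item 4 with one stating that:

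- dialysis dependence at discharge is analysed by a logistic regression of dependence on arm, adjusted for pre-existing non-dialysed chronic renal failure (yes/no) and for nephrotoxic drugs recorded at enrolment, whatever the observed balance;
- this is the analysis on which the endpoint is judged;
- the unadjusted chi-squared or Fisher result is reported alongside as a sensitivity analysis.

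Drug exposure after randomisation should not enter the model, because it may be affected by the assigned strategy. Baseline creatinine is a poor substitute for the yes/no covariate, because the section on acute renal failure allows it to be back-calculated when no pre-hospital value exists.

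The cost is one sentence of analysis wording. Comorbidities and nephrotoxic drugs are already collected, and sample size, enrolment, allocation and treatment do not change.
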